# Visit can be done remotely.

π If applicable.

1 Informed consent may be obtained after treatment. No data can be collected in the electronic case report form prior to consent. See section 2.3.3.

2 This is the baseline assessment and refers to the preinjury status.

3 Can be assessed remotely.

4 Images will be taken only if it is part of the local standard of care.

**Table 3 T3:** Study schedule for patients with clavicle hook plates.

Assessment parameters	Pre- intra- and postoperative visits								
	Visit 1	Visit 2	Post-implantation visits*			Visit 6^£^	Post hook plate removal visits**		
			Visit 3	Visit 4	Visit 5^£^		Visit 7**	Visit 8**	Visit 9^**^^,^^#^
	Screening/ preoperative	Intraoperative (Day 0)	2 (±1) weeks	6 (±1) weeks	3 months (±2 weeks)	Implant removal surgery (Day 0′)	6 (±1) weeks post-removal	3 months (±2 weeks) post-removal	12 (±1) months post-removal
Patient information/consent^1^	X								
Eligibility^1^	X								
Patient characteristics	X								
Surgical details		X							
Adverse events		X	X	X	X	X	X	X	X
Device deficiencies		X	X	X	X	X			
Bone healing^π^				X	X	X	X	X	X
Joint healing							X	X	X
Surgeons’ evaluation		X							
QuickDASH	X^2^		X	X	X	X^5^	X	X	X
Patient-reported outcomes^3^									
PROMIS upper extremity	X^2^		X	X	X	X^5^	X	X	X
Local pain			X	X	X	X^5^	X	X	X
Local discomfort			X	X	X	X^5^	X	X	X
Plate prominence			X	X	X	X^5^			
Implant removal						X			
Intraoperative shoulder stability						X			
Images (x-ray/CT scan)^4^	X	X	X	X	X	X	X	X	X

CT, computed tomography.

* All postoperative follow-up visits with the defined time windows are calculated from the day of surgical treatment (i.e., Day 0).

** All post-removal follow-up visits with the defined time windows are calculated from the day the hook plate is removed (i.e., Day 0′).

£ Whichever occurs first.

π If applicable.

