**Methods:**

Approximately 76 patients with clavicle fractures and primary surgical treatment with the 2.7 mm VA-LCP Clavicle Plate or 2.7 mm VA-LCP Clavicle Hook Plate will be enrolled prospectively over 15 months. Outcome measures include adverse events related/potentially related to the investigational device, clinical performance, functional outcomes (QuickDASH), PROs (PROMIS® upper extremity score, local pain, discomfort, and plate prominence), and radiographic outcomes. Data will be collected at baseline, 2w, 6w, 3m, 6m, 1y and 2y after surgery. The surgeons' experience with and perceived utility of the devices will be surveyed. Interim analysis will be performed when 30 patients per group have reached 6 months after surgery. Long-term outcomes will be evaluated using 2-year follow-up results. A Statistical Analysis Plan will be prepared before final analysis summarizing the descriptive statistics to be used.

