##### Follow-up schedule

2.3.4.5

Follow-up visits with defined time windows will be calculated from either the treatment day (Day 0) or the day of implant removal (Day 0′). All patients will be followed up for a maximum of 2 years after Clavicle Plates or Clavicle Hook Plates implantation. To ensure fair comparisons of treatment outcomes, the FU period is defined as follows:
▪For Clavicle Plates (shaft, lateral or medial), Day 0 is defined as the day of surgical treatment with the plate.▪For Clavicle Hook Plates, Day 0 is defined as the day of surgical treatment with the plate. Scheduled FU visits will be calculated from Day 0 until the plate is removed. After the plate is removed, the subsequent FU visits will be calculated from the day of removal (Day 0′)

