AEs will be reported both at patient level and AE level. The risk estimates will be presented along with the 95% Clopper-Pearson confidence interval. When calculating the AE rates, the denominator will be the full analysis population, irrespective of dropouts during FU. Sensitivity analyses will be conducted excluding patients who dropped out of the study and had not experienced an AE. For patients treated with Clavicle Plates, the risk of experiencing any ADE within 24 months after surgery will be reported. For the calculation of the ADE rate, only ADEs with onset before or within the upper visit window of the 24 months visit will be included. For patients treated with Clavicle Hook Plates, the risk of experiencing any ADE between surgical treatment and 12 months after removal of the Clavicle Hook Plate will be reported. Separate sub analyses on the risk of experiencing an ADE between surgery and Clavicle Hook Plate removal and within 12 months after the Clavicle Hook Plate removal will be performed. Separate ADE rates for the two FU periods including only ADEs with onset within the upper boundary of the visit window of the corresponding FU period will be calculated. For incidences of complaints related to plate prominence or discomfort and to local pain, incidence rates will be calculated, and summary statistics presented, including the number and percentage of patients with complaints related to plate prominence or discomfort (defined as NRS ≥1) and local pain (defined as NRS ≥3). For the reoperation rate due to ADE, fracture union rate, rate of stable AC joint healing at one-year post-removal, the full analysis population will be used as the denominator. Descriptive analyses on the rate of implants removed and the reasons for implant removal will be conducted. Simple summary statistics (i.e., numbers and percentages) will be produced for each bone healing category. QuickDASH, will be measured repeatedly during the FU period and analyzed using mixed effects models for repeated measures (MMRM). PROs also measured repeatedly during the FU period will likewise be analyzed using MMRM. For the surgeons' evaluation, simple summary statistics including numbers and percentages will be produced for each category.

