An interim analysis will be performed as soon as 30 patients in each group have reached the timepoint of 6 months after surgery. The main purpose of the analysis is to ensure safety, while the potential implications could include stopping the study, amending the protocol, or early dissemination of results, depending on the analysis of the study. Definition of the analysis populations will be specified in the SAP.

The planned statistical analysis will allow for repeated analyses on the per-protocol population in cases of major protocol deviations, as well as sensitivity analyses excluding patients who dropped out of the study and had not experienced an AE. Some degree of missing data is expected. Patients may withdraw from the study prior to completion of the intended FU for reasons such as death, severe intercurrent illness, withdrawal of consent, and loss to follow-up. In case of missing data a decision will be made whether special analysis methods are required to handle missing data on an individual basis for each endpoint (as defined in the SAP). This decision will be made based on the extent of the missing data and the likelihood of bias occurring because of the missing data, and the importance of the endpoint. Protocol deviations will be collected in the study database in a specific protocol deviation form and listed in the final analysis. All protocol deviations will be reviewed during the data review meeting prior to final analysis.

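### Hook-plate patients have no common 6-, 12- or 24-month time point after surgery, and a retained hook plate has no scheduled assessment after month 3, although the abstract promises these times for all patients

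*Protocol article*

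**What the plan says.** - **Abstract, Methods.** For the whole study: "Data will be collected at baseline, 2w, 6w, 3m, 6m, 1y and 2y after surgery". Also: "Long-term outcomes will be evaluated using 2-year follow-up results". Neither sentence distinguishes the two devices.
- **Table 2 (Clavicle Plates).** Visits at 6 (±1), 12 (±1) and 24 (±2) months after surgery.
- **Table 3 (Clavicle Hook Plates).** Visits at 2 weeks, 6 weeks and 3 months after implantation, then the removal surgery (Visit 6), then 6 weeks, 3 months and 12 (±1) months after removal (Visits 7 to 9). The footnote reads: "All post-removal follow-up visits with the defined time windows are calculated from the day the hook plate is removed". A £ footnote on Visits 5 and 6 says that the earlier of the two applies.
- **Section 2.3.4.5.** "All patients will be followed up for a maximum of 2 years after Clavicle Plates or Clavicle Hook Plates implantation". Section 2.3.3 gives the same maximum.
- **Section 2.4.1.** 30 patients per group, raised to 38 for 20% dropout, with that dropout placed at two years for both groups.
- **Section 2.4.2.** For hook plates, "the risk of experiencing any ADE between surgical treatment and 12 months after removal of the Clavicle Hook Plate will be reported", with separate rates before and after removal. The rate of stable AC joint healing one year after removal uses the full analysis population as denominator. Section 2.3.7.3 allows joint healing to be assessed only once the plate is out.
- **Section 2.4.2, interim.** The look is triggered once "30 patients in each group have reached the timepoint of 6 months after surgery". Its chief stated aim is a check on safety.

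**The concern.** The abstract gives one schedule and the hook-plate table another. After month 3, every hook-plate visit depends on a date that the plan does not fix and that may never occur.

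Two things are at stake. First, a hook-group result labelled 2-year would pool patients seen at different times since surgery, most of them possibly before two years. Second, the introduction names osteolysis, impingement and earlier removal as the problems that the new hook is meant to reduce. A hook left in place after month 3 is where they would be expected to show, and there the plan schedules no questionnaire, no pain, discomfort or prominence score and no adverse-event enquiry until removal. Section 2.3.7.6 lets high pain scores, and discomfort or prominence that needs treatment, generate adverse events. Without scheduled scores, those events are likely to be under-recorded.

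**Working it through.** **1. The plan's own figure.** 30 / (1 − 0.20) = 37.5, rounded up to 38 per group; 2 × 38 = 76. The enrolment figure reproduces. The issue is the two-year point to which the dropout is tied, not the arithmetic.

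**2. Fixed visits after surgery.** At 6, 12 and 24 months, Table 2 has 3 of 3 and Table 3 has 0 of 3.

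**3. Where removal-anchored visits fall.** Let R be the removal time in months after surgery. The documents give no R, so the values below are assumptions. Nominal dates are Visit 7 = R + 1.4 (6 weeks), Visit 8 = R + 3 and Visit 9 = R + 12. They are compared with Table 2's windows.

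| R | Visit 7 | Visit 8 | Visit 9 | In 6±1 | In 12±1 | In 24±2 |
|---|---|---|---|---|---|---|
| 3 | 4.4 | 6 | 15 | Visit 8 | none | none |
| 6 | 7.4 | 9 | 18 | removal visit | none | none |
| 9 | 10.4 | 12 | 21 | none | Visit 8 | none |
| 10 | 11.4 | 13 | 22 | none | Visits 7, 8 | Visit 9 |
| 12 | 13.4 | 15 | 24 | none | removal visit | Visit 9 |
| 13 | 14.4 | 16 | 25 | none | removal visit | Visit 9 |
| 18 | 19.4 | 21 | 30 | none | none | none |
| never | – | – | – | none | none | none |

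Solving for R:
- 6±1 months is reached for R of about 2 to 7 (Visit 8 for 2 to 4, Visit 7 for 3.6 to 5.6, the removal visit for 5 to 7).
- 12±1 months is reached for R of about 8 to 13 (Visit 8 for 8 to 10, Visit 7 for 9.6 to 11.6, the removal visit for 11 to 13), or through Visit 9 for R up to 1.
- Visit 9 reaches 24±2 months for 22 ≤ R + 12 ≤ 26, that is R from 10 to 14. A very late removal (R of 19 or more) can put an earlier post-removal visit or the removal itself there, but Visit 9 is then far past the cap.

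By nominal dates, no single removal time serves both the 6-month and the 24-month point.

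**4. The cap.** Nominal Visit 9 passes 24 months when R + 12 > 24, so R > 12. At the early edge of its ±1-month window the condition is R + 11 > 24, so R > 13.

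**5. Retained plates.** With no removal date:
- nothing is scheduled after month 3;
- the end of the adverse-device-effect window, removal plus 12 months, is undefined;
- a patient for whom AC joint healing applies stays in the full-population denominator but cannot enter the numerator, because joint healing is not assessed before removal.

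**The case against.** The strongest reply is that the re-anchoring is a declared design. Section 2.3.4.5 sets it out and gives fairness of comparison as the reason. Sections 2.3.7.2 and 2.4.2 define hook-group outcomes relative to removal. Table 3, unlike Table 2, does not mark removal as conditional, so it presumes that hook plates come out. Visit 6 collects adverse events, device deficiencies and the pre-removal questionnaires and scores. Unscheduled visits record related adverse events. Two years is a maximum, so an earlier end does not breach it. Figure 1 is not shown and may carry more schedule detail.

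Much of this stands, and it rules out four stronger readings that a reader might infer:

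- *The hook group has no 6-month or 2-year read-out at all.* Not supported. Six months in the interim rule is elapsed time that triggers a mainly safety-directed analysis. Related events can be counted to that date without a visit, and removal at about months 2 to 7 puts a visit nearby. Long-term hook outcomes exist, but relative to removal.
- *The target of 30 cannot be met.* Not supported. Section 2.4.1 ties the 30 to the patient's state once the injury has healed, which a 12-month post-removal visit can provide. The documents give no retention rate from which to count completers.
- *Problems after month 3 surface only through unscheduled contact.* True only for plates never removed; otherwise Visit 6 picks them up, though late.
- *The £ footnote cancels the removal visit when month 3 comes first.* Visits 7 to 9 depend on Visit 6, so the natural reading is that early removal replaces Visit 5. The wording needs clarifying, no more.

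The reply does not remove the conflict between the abstract and Table 3. Nor does it close the gap for retained plates: section 2.3.5 records only related adverse events at unscheduled visits, so no questionnaires or scores.

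**Conclusion.** The point holds as a contradiction to reconcile together with a gap in follow-up. The abstract's schedule and 2-year result, and the two-year dropout basis in section 2.4.1, do not match Table 3. QuickDASH, PROMIS and the numerical rating scores in the hook group have no common 6-, 12- or 24-month time point after surgery. For removal before about month 10, scheduled follow-up ends before a 24±2-month window opens. For removal after about month 13, the last visit lies beyond the cap. A plate in place after month 3 has no scheduled assessment until removal, and none if it is never removed; the adverse-device-effect window is then open-ended and the joint-healing rate is biased downwards for applicable patients.

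The schedule facts are read directly from the document. How many patients are affected depends on removal times and retention, which the document does not give, so no patient count is offered. No view is taken on when plates should be removed.

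**What to change.** 1. **Restate the claims.** In the abstract and section 2.4.1, say that the hook group's long-term read-out is 12 months after removal, at a variable time since surgery. In section 2.4.2, say that the 6-month interim trigger is elapsed time, not a visit.
2. **Cover plates still in place after month 3.** Add short remote contacts at 6, 12 and 24 months after implantation, collecting adverse events, implant status, QuickDASH, PROMIS and the rating scores. Table 3 already allows patient-reported outcomes to be taken remotely.
3. **Give the safety estimate an end.** Report hook adverse-device-effect risk by time since implantation, censored at last contact, alongside the planned rates before and after removal. State how retained plates count in the joint-healing rate.
4. **Tidy the schedule.** Reword the £ footnote on Visits 5 and 6, and reconcile the 2-year cap with the 12-month post-removal visit.

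The cost is one amendment and at most three short remote contacts for a subset of about 38 patients. Items 1 and 4 change wording only, although how the cap is reconciled may affect follow-up for late removals. With 43 patients enrolled so far, the contacts can still cover much of the group.

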# Visit can be done remotely.

1 Informed consent may be obtained after treatment. No data can be collected in the case report form prior to consent. See Section 2.3.3.

2 This is the baseline assessment and refers to the preinjury status.

3 Can be assessed remotely.

4 Images will be taken only if it is part of the local standard of care.

5 Refers to the status prior to the implant removal surgery.

**Figure 1 F1:**
[figure not shown]
Planned patient flow (adapted from STROBE).

Data from participating patients are documented in electronic CRFs and captured using the REDCap Cloud Electronic Data Capture system (https://www.redcapcloud.com/) (14, 15) to which only authorized personnel have access. After termination of the study, each site will receive an electronic copy of its own data. Based on the risk analyses, no data monitoring committee is planned. Regular data monitoring and cleaning will be performed to ensure data accuracy.

##### Baseline information

2.3.4.1

Demographic data include sex and year of birth, height, weight, and body mass index. Concomitant diseases will be assessed using the Charlson Comorbidity Index (16, 17).

##### Injury details

2.3.4.2

Injury details include the date of injury, side of injury, and type of injury. Clavicle fracture will be recorded using the AO/OTA classification (18) and the Robinson classification (19), and AC joint dislocation using the Rockwood classification (20).

##### Treatment details

2.3.4.3

Surgical details include:
▪Date of surgery when the fixation with a Clavicle Plate/Clavicle Hook Plate is performed.▪Surgical time (skin-to-skin time)▪Plate details (type of plate and size and material for Clavicle Plates, and type of plate, hook depth and material for Clavicle Hook Plates)▪Screw details▪Adjunctive fixation (osseous cerclage suture, direct ligament suture, internal brace, ligament augmentation for primary repair, suture anchors, muscular reattachment or other)▪Fluoroscopy time (in min)

##### Imaging data

2.3.4.4

Each site will take images per local SoC (routine) procedures. All images will be deidentified and sent to the sponsor.

##### Follow-up schedule

2.3.4.5

Follow-up visits with defined time windows will be calculated from either the treatment day (Day 0) or the day of implant removal (Day 0′). All patients will be followed up for a maximum of 2 years after Clavicle Plates or Clavicle Hook Plates implantation. To ensure fair comparisons of treatment outcomes, the FU period is defined as follows:
▪For Clavicle Plates (shaft, lateral or medial), Day 0 is defined as the day of surgical treatment with the plate.▪For Clavicle Hook Plates, Day 0 is defined as the day of surgical treatment with the plate. Scheduled FU visits will be calculated from Day 0 until the plate is removed. After the plate is removed, the subsequent FU visits will be calculated from the day of removal (Day 0′)

#### Unscheduled visits

2.3.5

Unscheduled visits outside of the defined timepoints may take place any time during the study in cases of medical emergency or if deemed appropriate for patient care. No data will be recorded in the eCRF except for any device or treatment related adverse events (AEs). Any images taken will be sent to the sponsor, and a drop out form will be completed if a patient drops out.

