#### Data collection

2.3.4

Tables 2, 3 show data to be recorded for Clavicle Plates and Clavicle Hook Plates. Figure 1 presents the planned patient flow.

**Table 2 T2:** Study schedule for patients with clavicle plates (lateral, shaft, and medial).

Assessment parameters	Pre- intra- and postoperative visits*							
	Visit 1	Visit 2	Visit 3	Visit 4	Visit 5	Visit 6	Visit 7^#^	Visit 8^#^
	Screening/preoperative	Intraoperative (Day 0)	2 (±1) weeks	6 (±1) weeks	3 months (±2 weeks)	6 (±1) months	12 (±1) months	24 (±2) months
Patient information/consent^1^	X							
Eligibility^1^	X							
Patient characteristics	X							
Surgical details		X						
Adverse events		X	X	X	X	X	X	X
Device deficiencies		X	X	X	X	X	X	X
Bone healing				X	X	X	X	X
Surgeons’ evaluation		X						
QuickDASH	X^2^		X	X	X	X	X	X
Patient-reported outcomes^3^								
PROMIS Upper Extremity	X^2^		X	X	X	X	X	X
Local pain			X	X	X	X	X	X
Local discomfort			X	X	X	X	X	X
Plate prominence			X	X	X	X	X	X
Implant removal^π^			X	X	X	X	X	X
Images (x-ray/CT scan)^4^	X	X	X	X	X	X	X	X

CT, computed tomography.

* All postoperative follow-up visits with the defined time windows are calculated from the day of surgical treatment (i.e., Day 0).

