##### Implant removal

2.3.7.7

The rate of implants removed during the study together with the reasons and timing of removal will be analyzed. Data collected include date of surgery and reason for removal. If the implant is removed due to an AE or device deficiency, this will be documented on the specific form. In patients with Clavicle Hook Plates, upon plate removal the stability of the shoulder ligaments will be assessed intraoperatively. The AC joint stability will be assessed as stable, partially unstable, or unstable.

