##### Device deficiencies

2.3.7.8

All device deficiencies will be reviewed, determined and documented in writing whether they could have led to a serious ADE.

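### The recording limit at unscheduled visits conflicts with the duty to document all device deficiencies, so a deficiency without a related AE can miss the database in two situations

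*Protocol article*

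**What the plan says.** **Unscheduled visits (2.3.5).** Visits outside the schedule may happen at any time for emergencies or patient care. The recording rule is exclusive: "No data will be recorded in the eCRF except for any device or treatment related adverse events (AEs". Two other items are kept: "Any images taken will be sent to the sponsor, and a drop out form will be completed if a patient drops out".

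**Device deficiencies (2.3.7.8).** "All device deficiencies will be reviewed, determined and documented in writing whether they could have led to a serious ADE". The sentence names neither the eCRF nor a type of visit.

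**Implant removal (2.3.7.7).** "The rate of implants removed during the study together with the reasons and timing of removal will be analyzed". On content: "Data collected include date of surgery and reason for removal". In addition: "If the implant is removed due to an AE or device deficiency, this will be documented on the specific form".

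**Schedules (2.3.4, Tables 2 and 3).** For Clavicle Plates, device deficiencies are marked at Visits 2 to 8 and implant removal, where applicable, at Visits 3 to 8. For hook plates, deficiencies are marked at Visits 2 to 6. Visit 6 is the removal surgery, with AEs, deficiencies and removal all marked.

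**Place of recording (2.3.4).** Patient data are documented in electronic CRFs. No other route is described.

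**The concern.** A device deficiency need not cause an AE, and a plate can be removed at the patient's request without one. The Discussion notes that many patients ask for removal for various reasons. Neither event is a related AE. Read literally, 2.3.5 therefore bars its entry when it comes to light at an unscheduled contact, although 2.3.7.8 wants every deficiency documented and 2.3.7.7 wants the rate, reasons and timing of removals.

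The study is meant to give first clinical evidence on the safety and performance of a new plate system. Deficiencies are part of that evidence. A recording rule that can drop them makes the device look better than it is and never worse.

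**Working it through.** No figure in the protocol depends on this point. The check sets the recording rules beside the visit schedule and follows each type of event to its first possible entry.

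**1. The plan's own sample size, for scale.** 2.4.1 wants 30 patients per group and assumes 20% dropout at two years: 30 / (1 − 0.20) = 37.5, rounded up to 38 per group, or 76 in total. This agrees with the stated figure.

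**2. What 2.3.5 lets in.** A deficiency that causes a related AE can be entered. So can a complaint that 2.3.7.6 classes as an AE, if it is device- or treatment-related: pain NRS of 5 or more, or discomfort or prominence that requires treatment. What stays out is a deficiency without a related AE and a removal without a related AE.

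**3. Wait until the next scheduled entry, Clavicle Plates (Table 2).** Longest wait = (later visit + its window) − (earlier visit − its window), in months, with 2 weeks taken as 0.5 month.

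| Interval | Nominal wait | Longest wait with windows |
|---|---|---|
| 3 to 6 months | 3 | (6 + 1) − (3 − 0.5) = 4.5 |
| 6 to 12 months | 6 | (12 + 1) − (6 − 1) = 8 |
| 12 to 24 months | 12 | (24 + 2) − (12 − 1) = 15 |

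A patient who attends the later visit has the event recorded there. A removal keeps its true date and reason, because those are the items collected. A patient who leaves during the wait has no stated entry route: the dropout form (2.3.6) records the reasons for termination, and the data are censored on that day.

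**4. Hook plates (Table 3).**
- Removal is Visit 6, so it is a scheduled entry and 2.3.5 does not apply to it.
- While the plate is in place, the last scheduled visit is at 3 months. If the plate stays in longer, nothing is scheduled until removal, so the wait has no fixed end. If removal does not take place during participation (at most 2 years), no later scheduled entry follows.
- The deficiency row stops at removal, which is not a gap: Visit 6 records deficiencies, and afterwards the plate is gone.

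**5. Do the items that are kept close the gap?** Images go to the sponsor, but they are taken only under local standard of care, and neither implant damage nor device deficiency is among the central reading parameters in 2.3.7.9.

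**6. Result by event type.**

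| Event first seen at an unscheduled visit | Outcome under the text |
|---|---|
| Deficiency with a related AE | The AE can be entered at once |
| Deficiency without a related AE, Clavicle Plate | Late; missed if the patient leaves first |
| Deficiency without a related AE, hook plate beyond 3 months | Waits for removal; missed if the patient leaves, or is not re-implanted into the schedule by a removal visit, before participation ends |
| Clavicle Plate removal without a related AE | Late; lost if the patient leaves first |
| Hook plate removal | Not affected (Visit 6) |

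**7. Scale.** One missed event is 1/38 = 2.6 percentage points of an enrolled group, or 1/30 = 3.3 points of the 30 patients wanted at the end. The assumed dropout is 0.20 × 38 = 7.6, so 7 to 8 patients per group. That is everyone expected to leave, for any reason. Those affected are the patients who also had such an event at an unscheduled visit and left before the next scheduled one, and the documents give nothing from which to estimate that share.

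**The case against.** The strongest reply is that the two sections can both be obeyed. 2.3.5 governs what is entered in the eCRF at one kind of visit, while 2.3.7.8 asks for documentation in writing and could be met outside the eCRF. Deficiencies are asked for again at scheduled visits, removals due to an AE or deficiency have their own form, and Clavicle Plate Visits 7 and 8 may be remote, which makes later entry easier. The text is also an article that condenses a fuller protocol, and its supplement on collected events is not shown.

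Much of this stands. It shows that most events are recorded late rather than lost, and the full protocol or the eCRF may already allow these forms at any time. Two things remain. The article names the eCRF as the place for patient data and describes no other route that would bring a deficiency into the analysis. And 2.3.5 is not silent on a detail left to another document: it states a prohibition with a closed list of exceptions.

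A reader might go further and infer that implant removals in general are under-counted, or that 7 to 8 patients per group are affected. The documents support neither. Hook plate removal is a scheduled visit, Clavicle Plate removal is asked for at every postoperative visit, and removals for treated prominence or discomfort or for severe pain involve complaints that count as AEs. The 7 to 8 patients are the whole assumed dropout.

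**Conclusion.** The point holds in a limited form. For device deficiencies without a related AE, 2.3.5 conflicts with 2.3.7.8. Followed as written, it can keep such a deficiency out of the database when the patient drops out before the next scheduled visit, or when a hook plate stays in beyond 3 months. For Clavicle Plate removals without a related AE, the usual effect is delay, with loss only if the patient leaves first. Hook plate removals are unaffected.

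The direction is certain: only under-counting is possible. The size is unknown and may well be small. The conclusion assumes that sites apply 2.3.5 literally and that no separate deficiency log feeds the analysis. If the full protocol provides such a route, what remains is a sentence to correct in the article.

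**What to change.** Reword the exception in 2.3.5 to: *except device- or treatment-related AEs, device deficiencies, and implant removal (date and reason)*. Make those existing forms available at unscheduled visits in the eCRF. This brings 2.3.5 into line with 2.3.7.7 and 2.3.7.8 and changes neither the visit schedule nor patient care.

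The cost is one sentence, access to existing forms and slightly more data entry at sites. The article reports 43 patients enrolled of the 76 planned, so a change now can still protect the data of later patients. For those already enrolled, sites could be asked whether any deficiency or removal seen at an unscheduled visit was left out.
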